**6 – METHODOLOGY**

## **6.1. Ethical aspects**

## This research project will follow the recommendations of the “consort” (consolidated standards of reporting trials). The research volunteers will be duly clarified and informed about the risks, methods and objectives of this project, being necessary the signature of the free and informed consent term – tcle (Annex I), in accordance with the Helsinki Declaration.41

## All information to be collected will have an exclusively scientific purpose and the identity of the volunteers will be preserved. Participation in the study may be canceled and the consent form withdrawn at any time during the research, ensuring the confidentiality of the volunteer's confidentiality even in case of abandonment of treatment.

## **6.2. Sample selection**

Fifty volunteers aged between 18 and 29 will be selected, who must follow the inclusion and exclusion criteria described in table 1. The clinical evaluation of the volunteers will be carried out through anamnesis, intraoral clinical examination and color registration. All participants will undergo prophylaxis performed with a rubber cup (Microdon, SP, Brazil) and pumice stone (Biodinamic, PR, Brazil) seven days before the start of the study and will receive oral hygiene kits, to be used throughout the treatment, for the standardization of a toothpaste that does not have a desensitizing action and that does not contain fluor, in order to mitigate possible interferences in the evaluation of this study. The kit will consist of a toothbrush (Oral B, Cerdas Indicator, São Paulo, SP, Brazil) and a toothpaste (My First Colgate®, Colgate-Palmolive Company, SP, Brazil), under instructions for use three times a day.

Table 1: Inclusion and exclusion criteria.

| ***INCLUSION CRITERIA*** | ***EXCLUSION CRITERIA*** |
| --- | --- |
| - Shade greater than A2 in upper incisors and canines, according to the Vita Classical shade guide; - Absence of active caries lesions; - Patients who have never undergone bleaching therapy - Present good oral hygiene; - Not presenting hypersensitivity to tactile and evaporative stimuli through the Visual Analog Pain Scale; - Not being a smoker; - Not being pregnant; | - Patients undergoing fixed orthodontic treatment; - Non-vital teeth with darkening; - Presence of cracks or fractures; - Patients allergic to the product; - Extensive restorations in molars; - Presence of gastroesophageal dysfunctions; - Presence of dentinal exposure in anterior and/or posterior teeth; - Patients over 30 years of age. |

## **6.3. Study design**

## This clinical trial will be randomized, placebo-controlled and blinded. To determine the groups, a randomization process will be carried out to determine the treatment to be applied. Patients will be randomized and randomly divided into two groups: G1- Placebo; G2 – Potassium Oxalate; as described in figure 1.

Evaluated Patients (N=X)

Excluded Patients Y=(X-50)

**Recruitment**

Randomization by lottery (N=50)

Whitening treatment

Polanight 22% Carbamide Peroxide (SDI)

**Follow-up**

**G1 (n=25)**

Placebo

(fluoride-free toothpaste)

**G2 (n=25)**

Experimental Group

(1.5% Potassium Oxalate)

Pain assessment by daily questionnaire

(n=50)

**Analysis**

**Figure 1: Study design**

All groups will undergo home bleaching treatment with 22% Polanight carbamide peroxide (SDI). Only the G2 group will receive desensitizing treatment with 1.5% potassium oxalate gel (Table 2). Volunteers will be instructed on the use of whitening treatment and treatment with placebo or desensitizing.

**Table 2.** Division of groups, bleaching treatment, desensitizing treatments.

| ***GROUPS (N=50)*** | ***BLEACHING TREATMENT*** | ***DESENSITIZING TREATMENT*** |
| --- | --- | --- |
| **G1** |  | ---- |
| **G2** | Pola Night CP 22%  (SDI) | 1.5% Potassium Oxalate (Painless, BM4,SC, Brazil) |

**6.4. Randomization**

The randomization process will be carried out by numerical drawing by the main researcher. A number will be assigned to each experimental group (1 for G1, 2 for G2) and a lottery will be performed for each volunteer. Patients will be numbered according to the enrollment sequence.

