**6.5. Blinding**

In this double-blind study, the participant will be unaware of the desensitizing treatment he will receive, as both the desensitizing gel and the placebo gel will be placed in the same container to make their identification impossible. The texture, color and odor of the placebo will be similar to 1.5% potassium oxalate (Painless, BM4, SC, Brazil). The pain sensitivity evaluator will also be unaware of the group to which the participant will belong, because he will not participate in the randomization process. The research will have a single operator, who will perform the experimental part.

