## **6.10. Sensitivity assessment**

## Postoperative sensitivity will be evaluated through a daily questionnaire that will be provided to volunteers from the first at-home bleaching treatment session, which must be completed during the 21 days of treatment, according to their personal perception and pain threshold, on the level of sensitivity or discomfort caused by the bleaching treatment, on a scale from 0 (no pain) to 10 (severe pain), according to Visual Analogue Scale.

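### No allocation concealment is described for the main researcher's draw, and neither the single operator nor the colour measurer is stated to be masked

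*Protocol*

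**What the plan says.** **Allocation (Protocol, section 6.4).** "The randomization process will be carried out by numerical drawing by the main researcher". Number 1 stands for G1 and number 2 for G2, and "a lottery will be performed for each volunteer". The section adds: "Patients will be numbered according to the enrollment sequence". Figure 1 shows 50 randomised, 25 to each group. No concealment step is described here or elsewhere.

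**Masking (section 6.5).** The trial is called double-blind. Of the volunteer it says that "the participant will be unaware of the desensitizing treatment he will receive"; the means are the same container and a placebo matched in look, feel and smell. The pain evaluator is also masked, "because he will not participate in the randomization process". The section then says: "The research will have a single operator, who will perform the experimental part". It does not say whether that operator is masked.

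**Outcomes.** Pain (section 6.10) is the volunteer's own daily score from 0 to 10, given "according to their personal perception and pain threshold". Colour (section 6.9) is read with a spectrophotometer. The person who takes the reading is not named and no masking is stated.

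**Kits (section 6.6).** Each volunteer receives an unmarked tube. No kit code is mentioned.

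**The concern.** Allocation concealment and masking of staff are matters for the protocol, and an analysis plan cannot restore them afterwards. Three routes to bias are left open:

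- **Selection at allocation.** The drawer sees each result, and nothing described would expose a repeated draw or a changed order.
- **Cues to the volunteer.** Pain is self-scored, so its protection rests on the volunteer's ignorance of the group. Whoever hands over the kit and instructs can weaken that if he or she knows the allocation.
- **Colour measurement.** H02 compares colour change between the groups, with no stated masking of the measurer.

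Participant masking also depends on the comparator being what section 6.5 says it is, and other parts of the protocol describe it differently.

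**Working it through.** The protocol states no figure on this point that could be reproduced. The check is mainly textual, with one calculation on the draw.

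**Step 1: who is masked, by role.**

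| Role | Stated in the protocol |
| --- | --- |
| Participant, who scores pain | Masked (6.5), matched gel (6.5, 6.6) |
| Pain evaluator | Masked, because not involved in randomisation (6.5) |
| Main researcher | Draws the lots (6.4); by the reasoning of 6.5, not masked |
| Single operator | Masking not stated (6.5) |
| Colour measurer | Neither the person nor masking stated (6.9) |
| Whoever hands over kits and instructs | Not stated (6.3, 6.6) |

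Because the participant rates pain at home, masking a separate evaluator adds little for that outcome. The masking that counts for pain is the participant's.

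**Step 2: what the participant's masking rests on.** The descriptions of what G1 receives do not agree:

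- Figure 1: fluoride-free toothpaste as placebo.
- Table 2: dashes in the desensitising column for G1.
- Sections 6.5 and 6.6: a placebo gel matched to the active gel.
- Section 6.6, kit list: a potassium oxalate tube in the volunteer's kit, with no placebo tube listed.
- Section 6.6, instructions: both the placebo paragraph and the oxalate paragraph refer to group 1.

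These passages must be reconciled. This review does not say which is right.

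**Step 3: does the draw fit 25 per arm?** Inputs: N = 50 and 25 per arm (Figure 1), one lot per volunteer (6.4). Assume first that the lots are independent with probability 1/2:

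- P(exactly 25:25) = C(50,25) / 2^50 = 0.112
- P(28:22 or more uneven) = 2 × P(X ≥ 28) = 0.480
- P(30:20 or more uneven) = 2 × P(X ≥ 30) = 0.203

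with X binomial(50, 1/2). A guaranteed 25:25 split therefore needs a restricted draw, which section 6.4 does not describe.

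**Step 4: predictability if the draw is restricted.** Assume an urn of 25 + 25 lots drawn without replacement, with someone who sees past draws and always guesses the group with more lots left:

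- Expected correct guesses = 25 + (1/0.11228 − 1)/2 = 25 + 3.95 = 28.95, about 29.0 of 50, against 25 by chance.
- Expected number of final allocations known with certainty = 2 × 25/26 = 1.92, about 1.9.

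This is a modest gain. With independent lots there is no such gain, and an unrecorded redraw is then the main route.

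**The case against.** The strongest reply is that section 6.5 already describes an ordinary double-blind trial. The participant is the one who scores pain, and the participant is masked with a matched gel in the same container. That stands as far as the stated intention goes. A reader might infer that only the pain evaluator is masked, or that pain scores are unprotected. Section 6.5 contradicts the first. The second does not follow, because what remains for pain is indirect: cues from staff who may know the group, and the unreconciled comparator.

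Other tempting inferences also go further than the text:

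- **The draw takes place at enrolment.** Section 6.4 gives a draw per volunteer and numbering by enrolment order, but not when the draw is made.
- **The operator is the main researcher, or does everything including colour.** Section 6.5 gives the operator the experimental part and says no more.
- **The drawer can steer who is enrolled next.** This needs the drawer to enrol or to share coming allocations, and neither is stated.
- **Colour is measured unmasked.** The protocol is silent on this. An instrument reading is also less open to expectation than a visual shade match, so the risk is smaller, though probe placement leaves some.
- **Unmarked tubes make the gel untraceable.** The word fits the masking aim and does not exclude a number on the kit. It is only true that no code is described.

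The conflicting comparator passages could be drafting slips. They still need correcting, because the masking claim depends on them. None of these replies supplies a concealment step or states masking for the operator or colour measurer.

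**Conclusion.** The point holds in a limited form. The protocol assigns the draw to the main researcher with no concealment described, and it states no masking for the single operator or the colour measurer. The exposure is all 50 allocations known to the drawer, and H02 without stated assessor masking. For pain, participant masking is stated, so the double-blind claim is not refuted, but it is not secure until the comparator passages agree.

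No size of bias on pain or colour can be derived from the documents, and none is claimed. The figures of 0.112 for independent lots and about 29 of 50 for an urn describe the draw only, and each rests on its assumed mechanism. This is an inexpensive improvement that should be made before enrolment, not evidence that bias will occur.

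**What to change.** 1. Reconcile Figure 1, Table 2, section 6.5 and section 6.6 on what G1 receives, what the kit contains and which group each instruction addresses.
2. Before enrolment, have someone who does not enrol, instruct or measure generate a 25:25 random list and keep it. This can be an existing team member, the gel supplier or a dispensing pharmacy.
3. The same person packs the two gels, as finally described, into 50 identical tubes numbered 1 to 50 according to the list.
4. Issue kits strictly in enrolment-number order.
5. State in section 6.5 that the operator, the colour measurer and the analyst see only the kit number until the data are locked, and name the colour measurer's role in section 6.9.
6. In section 6.6, change the unmarked tube to a tube marked only with its kit number.

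The cost is generating one list, labelling 50 tubes and rewording the protocol. The small downside is that the main researcher gives up the draw if he or she enrols, treats or measures.

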**6.5. Blinding**

In this double-blind study, the participant will be unaware of the desensitizing treatment he will receive, as both the desensitizing gel and the placebo gel will be placed in the same container to make their identification impossible. The texture, color and odor of the placebo will be similar to 1.5% potassium oxalate (Painless, BM4, SC, Brazil). The pain sensitivity evaluator will also be unaware of the group to which the participant will belong, because he will not participate in the randomization process. The research will have a single operator, who will perform the experimental part.

**6.6 Intervention**

Each volunteer in the group will receive a kit containing a tube with Polanight bleaching agent (SDI, SP, Brazil), two individual trays of ethylene/vinyl acetate copolymer (upper and lower), an unmarked tube with the desensitizer (potassium oxalate at 1.5%), a toothbrush and a fluoride-free toothpaste (My First Colgate®, Colgate-Palmolive Company, SP, Brazil).

*-Dental whitening*

The volunteers will be molded with alginate (Jeltrate Plus - Dentsply) with the aid of a tray (Tecnodent). Then, the models will be made using special plaster (Durone-Dentsply). The trays will be made from the models obtained using an ethylene/vinyl acetate copolymer (FGM) plate and a vacuum plasticizer (Plastivac P7/Bio Art). It will be recommended to apply a drop of the whitening agent Polanight (SDI, SP, Brazil) on each corresponding tooth in the tray that should be used for 45 minutes a day for a period of twenty one days.

- *Placebo*

After the bleaching treatment, the trays will be washed with running water, and the volunteers in group 1 will apply a small amount of the placebo gel, without active ingredient, with a color, texture and odor similar to 1.5% oxalate gel (Painless, BM4, SC, Brazil) in the spaces related to the buccal portions of the teeth of the trays, which should be used for 10 minutes. After removing the tray, the patient should brush the teeth with the fluoride-free toothpaste (My First Colgate®, Colgate-Palmolive Company, SP, Brazil).

*- Treatment with 1.5% Potassium Oxalate*

After the bleaching treatment, the trays will be washed with running water, and the volunteers in group 1 will apply a small amount of 1.5% oxalate gel (Painless, BM4, SC, Brazil) in the spaces related to the buccal portions of the teeth of the teeth trays, which should be used for 10 minutes. After removing the tray, the patient should brush their teeth with fluoride-free toothpaste (My First Colgate®) and clean the tray in order to remove all the gel inside the tray.

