**RESEARCH PROJECT**

**5 – OBJECTIVE**

This randomized, placebo-controlled clinical trial aims to evaluate the effect of 1.5% potassium oxalate in controlling pain sensitivity and color change after at-home tooth whitening. The null hypotheses tested in the present study will be: H01 - There will be no difference in tooth sensitivity between the groups bleached with 22% carbamide peroxide associated or not with 1.5% potassium oxalate, thirty days after the end of treatments.

H02- There will be no difference in color change between the groups bleached with 22% carbamide peroxide associated or not with 15% potassium oxalate, thirty days after the end of treatments.

H03- Use of 1.5% potassium oxalate after bleaching treatment will not influence Health-Related Quality of Life (HRQoL).

H04- Use of potassium oxalate after bleaching treatment will not influence patient satisfaction.

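### Section 6.6 assigns both gels to group 1, gives group 2 none and lists no placebo tube, and Figure 1 names a different control product from sections 6.5 and 6.6

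*Protocol*

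**What the plan says.** **Arm definitions.** Section 6.3 labels G1 as placebo and G2 as potassium oxalate. Section 6.4 ties the lottery numbers to those labels (1 is G1, 2 is G2). The text above Table 2 states: "Only the G2 group will receive desensitizing treatment with 1.5% potassium oxalate gel".

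**Application steps (section 6.6).** Under the placebo heading, "volunteers in group 1 will apply a small amount of the placebo gel, without active ingredient". Under the oxalate heading, "volunteers in group 1 will apply a small amount of 1.5% oxalate gel". No sentence in section 6.6 addresses group 2.

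**Kit (section 6.6).** The paragraph begins "Each volunteer in the group will receive a kit containing a tube with Polanight bleaching agent". Among the contents is "an unmarked tube with the desensitizer (potassium oxalate at 1.5"%). No placebo tube and no second kit are described.

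**Control product.** The G1 box of Figure 1 gives the placebo as "fluoride-free toothpaste". Sections 6.5 and 6.6 describe a gel that resembles the oxalate gel in appearance and smell, and section 6.5 has it supplied in the same container. In section 6.6 the toothpaste is also a kit item, and participants brush with it after tray removal under both treatment headings.

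**Minor items.** Table 2 shows only a dash for G1 in the desensitizing column. H02 in section 5 reads "associated or not with 15% potassium oxalate, thirty days after the end of treatments", whereas every other place in the protocol that states a strength for the study gel gives 1.5%.

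**The concern.** The only randomized difference in this trial is which gel goes into the tray after bleaching, with 25 participants planned per arm. Section 6.6 is where that difference becomes an instruction to participants, and there it disagrees with the arm definitions. An error in which gel a participant received cannot be put right in the analysis. A participant would be unlikely to notice one either, because the tube is unmarked and the gels are meant to look alike.

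The identity of the control matters for a related reason. Sensitivity is a daily self-rating from 0 to 10 (section 6.10), so the result depends on participants not knowing their arm. Section 6.5 rests that blinding on a look-alike gel. If the control is instead the toothpaste that everyone also brushes with, the protocol does not explain how the two tubes would be made alike.

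**Working it through.** No sample size, power or error-rate figure is involved, so the check sets the statements side by side.

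**Step 1. Which group uses which gel?**

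| Source | Group 1 | Group 2 |
| --- | --- | --- |
| Section 6.3, arm labels | placebo | oxalate |
| Figure 1 | placebo (toothpaste) | oxalate |
| Text above Table 2 | no oxalate | oxalate |
| Section 6.6, placebo paragraph | placebo gel | not mentioned |
| Section 6.6, oxalate paragraph | oxalate gel | not mentioned |

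Section 6.4 uses the same numbers for the draw, so group 1 in section 6.6 cannot be treated as a loose label. The last row contradicts the first three.

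**Step 2. What does the kit list imply?** The paragraph refers to each volunteer in the group without saying which group. There are three possible readings:

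- It covers all participants. Then controls receive oxalate.
- It covers one arm. Then the other arm's kit is not described.
- It describes a blinded tube that may hold either gel. Then the placebo alternative has been left out of the text.

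The paragraph needs correcting under each of them.

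**Step 3. What contrast follows from each literal reading?** Code oxalate use as 1 and no oxalate as 0, and subtract group 1 from group 2.

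| Reading | Group 2 − Group 1 |
| --- | --- |
| Sections 6.3 and 6.4, Figure 1 | 1 − 0 = 1 |
| Kit list, if it covers everyone | 1 − 1 = 0 |
| Application paragraphs as written | 0 − 1 = −1 |

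The contrast is therefore as intended, absent or reversed, depending on which part of the text is followed. This lists what the words imply. It does not forecast what would happen.

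**Step 4. What is the control?** Figure 1 says toothpaste; sections 6.5 and 6.6 say a gel with no active ingredient. Section 6.6 names the toothpaste separately from the placebo gel within the same paragraph, the gel in the tray and the toothpaste for brushing afterwards. As written, these are two products.

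**Step 5. Strength.** The figure of 15% occurs once, in H02. The introduction, H01, H03, Figure 1, Table 2 and sections 6.5 and 6.6 give 1.5%. No application step or product description uses 15%.

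**The case against.** The strongest reply is that the design is not really in doubt. Sections 6.3 and 6.4, the G2 box of Figure 1 and the sentence above Table 2 all point the same way, and section 6.5 describes two look-alike gels. The second mention of group 1 sits under a heading that names the oxalate treatment, in a paragraph that largely repeats the one before it, so it reads as a copying slip. This stands as far as intent goes: a reader who infers that the treatment contrast is unknowable goes too far. It does not supply a kit description for the placebo arm or settle what the placebo is.

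Several stronger readings are tempting and are not supported:

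- **A no-treatment control.** The Table 2 dash is in a column for desensitizing treatment, and a placebo is not a desensitizer. The text above the table mentions placebo use. G1's bleaching cell is also blank although both groups bleach, so the table layout may have been lost in conversion.
- **A ten-fold dose conflict.** One figure in a null hypothesis, used in no instruction, is an inconsistency to reconcile. It is not evidence of two competing regimens.
- **Oxalate in every kit.** The wording about the group is ambiguous, as step 2 shows.
- **A toothpaste control necessarily unblinds.** The documents do not exclude a toothpaste-based product in the same container. What they show is that the control is not consistently identified.
- **A calculable dilution of the effect.** That would need the fraction of controls who used oxalate, and the documents give none.

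Nor does the protocol say who packs the kits or from which text. Section 6.5 says only that a single operator carries out the experimental part.

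**Conclusion.** The point holds as a contradiction in the operative text. Section 6.6 gives group 1 two gels and group 2 none, describes a kit with oxalate and no placebo, and together with section 6.5 disagrees with Figure 1 on the control product. Followed literally, it would give controls oxalate or leave the oxalate arm without instructions. The intended comparison, G1 placebo against G2 oxalate, remains recoverable from the other sections.

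The size is the count of conflicts; no numerical bias is claimed. The conclusion assumes that section 6.6 is the text from which kits and participant instructions would be drawn. No other section gives that detail, but the protocol does not state it. The 15% in H02 and the unnamed placebo in Table 2 are minor by comparison.

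**What to change.** Reconcile section 6.6 and the G1 box of Figure 1 with sections 6.3, 6.4 and 6.5 and the text above Table 2, so that:

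- each arm number maps to one gel in both application paragraphs;
- the kit list describes each arm's tube separately;
- one control product is named and used throughout, and is distinguished from the brushing toothpaste.

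As minor items, name the placebo in Table 2 and reconcile the strength in H02 with the strength given elsewhere. The sponsor should confirm which statements are intended; this review does not choose among them.

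The cost is a wording amendment in a few places and a check of the packing list before kits are issued. If kits have already gone out, the sponsor should also confirm from dispensing records what each arm received. Sample size, visits and analysis are unaffected.

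### Section 6.6 writes a final tray-cleaning step for the oxalate arm only, so the two home procedures, read literally, differ by more than the gel

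*Protocol*

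**What the plan says.** Section 6.6 of the protocol gives each volunteer one upper and one lower tray. The bleaching agent is loaded into the trays, which "should be used for 45 minutes a day for a period of twenty one days". Two separate paragraphs then describe what follows in each arm.

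Both open with the same words: "After the bleaching treatment, the trays will be washed with running water". Both then have the volunteer load a little study gel, wear the tray for 10 minutes, remove it and brush.

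The placebo gel is described as "without active ingredient, with a color, texture and odor similar to 1.5% oxalate gel". For this arm the procedure stops at brushing: "After removing the tray, the patient should brush the teeth with the fluoride-free toothpaste". The oxalate paragraph has the same brushing step and continues: "and clean the tray in order to remove all the gel inside the tray".

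The text under Figure 1 in section 6.3 reserves the oxalate gel for G2 and names no other planned difference between the groups. On instructions it says only this: "Volunteers will be instructed on the use of whitening treatment and treatment with placebo or desensitizing".

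**The concern.** A placebo control isolates the active ingredient only if everything else that participants are told to do is the same. Here one arm has a written handling step that the other lacks, and it concerns the device that delivers the bleaching agent.

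That matters because H01 (tooth sensitivity) and H02 (colour change) both concern effects of bleaching carried out in that tray. If tray handling differed systematically by arm, a between-arm difference in either outcome, or the absence of one, could no longer be attributed to oxalate alone. No analysis could separate the two afterwards, because the handling step would coincide exactly with the allocated arm.

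This is not a detail that a statistical analysis plan would settle, since such a plan does not govern home-use instructions.

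**Working it through.** No arithmetic applies. The check sets the two paragraphs of section 6.6 side by side and then looks for a common instruction elsewhere in the protocol.

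| Step in the session | Placebo paragraph | Oxalate paragraph |
| --- | --- | --- |
| Wash tray with running water after bleaching | yes | yes |
| Load study gel in the tray | yes (placebo gel) | yes (oxalate gel) |
| Wear for 10 minutes | yes | yes |
| Remove tray and brush with fluoride-free toothpaste | yes | yes |
| Clean the tray of all remaining gel | not mentioned | yes |

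1. **Number of differences.** Apart from the gel itself, the written procedures differ at one step, the last.

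2. **Does the shared wash cover it?** No. In both paragraphs the wash comes after the bleaching gel and before the study gel. It removes what bleaching left behind. It cannot remove study gel that has not yet been loaded.

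3. **Does another section cover it?** No. Section 6.3 says that volunteers will be instructed but gives no content. Section 6.5 deals with containers and with the texture, colour and odour of the gels. No section gives an end-of-session cleaning step for both arms.

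4. **Is the tray used again?** Bleaching runs daily for 21 days with one pair of trays. Section 6.6 does not state how often the study gel is used. On the natural reading that it follows each daily session, the next thing placed in the tray is the following day's bleaching agent, and only the oxalate paragraph writes a step between the two.

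5. **Is the difference intended?** Nothing suggests so. Section 6.3 confines the contrast to the gel. The oxalate paragraph also contains a plain error, "the volunteers in group 1 will apply a small amount of 1.5% oxalate gel", although oxalate is G2 in section 6.3, Figure 1 and Table 2. The kit description in 6.6 mentions an oxalate tube and no placebo tube.

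**The case against.** The strongest reply is that this is an omission in loosely edited text. The two paragraphs are close copies, the oxalate one carries the wrong group number, and a lost final clause is weak evidence of a planned difference. That stands, and it is why the point is put as an inconsistency to reconcile and not as a deliberate design choice.

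Several stronger readings are tempting, and the documents do not support them.

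- A reader might infer that placebo participants put bleaching agent into an uncleaned tray. The protocol does not say so. The placebo paragraph is silent: it neither asks for cleaning nor rules it out.
- A reader might infer that leftover placebo gel would weaken bleaching and so lower both sensitivity and colour change in that arm. The documents say nothing about whether residue would persist to the next day or affect the bleaching agent, and the gel in question has no active ingredient. Neither the direction nor the size of a bias can be derived.
- A reader might count the sessions that follow a gel application and treat that as a measure of the problem. It would be a count of sessions, not of exposure or effect, and would assume that no placebo participant ever cleans a tray.
- A reader might infer that masking is broken. Section 6.5 promises that "the participant will be unaware of the desensitizing treatment he will receive". Each participant receives one set of instructions, and a cleaning step does not by itself reveal what the tube contains. Section 6.5 claims blinding for the participant and the pain evaluator, not for the operator. No arm-specific handout is described.

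What survives is narrower. The written procedures differ, and no other section removes the difference.

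**Conclusion.** The point holds as an inconsistency in the written procedure. Section 6.6 gives the arms different end-of-session instructions, the shared wash does not cover the gap, and this conflicts with the gel-only contrast in section 6.3. If carried out literally, it would add a second difference between the arms and could confound the sensitivity and colour comparisons.

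The extent is one step in the home procedure. Its effect on the results cannot be sized from the documents and may be nil. The conclusion that the arms could differ in practice rests on two assumptions: that the study gel follows each bleaching session, and that the instructions given to volunteers mirror section 6.6. If both arms are in fact told the same thing, only the protocol wording is at fault.

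The correction is worth making because it removes an avoidable alternative explanation at almost no cost.

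**What to change.** Replace the two arm-specific paragraphs of section 6.6 with one home procedure for all volunteers, identical in every word apart from the coded tube. In the same edit, correct the group number in the oxalate text. The tray-handling step after the 10-minute gel should read the same for both arms; which step that is, the investigator decides. Issue one instruction sheet, drawn from that text, to all 50 volunteers.

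The cost is about one sentence in section 6.6 and a single sheet. It needs no extra visits, staff or participants, and no change to the outcomes or the analysis.
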